### Adverse events reporting

Data on adverse events will be collected and reported via the Health Research Authority safety reporting for non-CTIMP studies guidance
^
132
^. We will specifically enquire about adverse events at each of the participant visits. All adverse events will be recorded. Participants will be asked to contact the study team about any adverse events they experience in-between face to face visits. Serious adverse events will be reported to the Sponsor and REC within 24 hours.

In addition to reporting all adverse events in line with the requirements of this protocol, the study team will be recording adverse events separately. These AEs will be transferred to Worldwide Clinical Trials for adding into a safety database, managed by both Worldwide Clinical Trials and COMPASS Pathways, allowing for the continued development of safety data around psilocybin.

We require consent from any participants to additionally share anonymised adverse event information with COMPASS Pathways, who will provide the study drug.

### Analysis

**
*Statistical measures*
**

Pre-post changes analysed using paired t-tests. Alpha will be set at 0.05. Any clinical data will be presented descriptively without comparison. Multiple comparisons will be post-hoc corrected.

**
*Qualitative analysis*
**

Free text transcriptions from the qualitative interviews will be thematically analysed. Each transcript will be independently coded by two researchers. The agreed codes will be aggregated using NVivo 14.0. An inductive method will be employed to establish emergent themes from the codes. Coverage (% of total data) for each theme will be calculated.

**
*Functional neuroimaging*
**

Analysis of the neuroimaging data will take place using the KCL Neuroimaging Network and the Rosalind cluster. fMRI analysis will be carried out within Statistical Parametric Mapping software using a seed-based approach implemented in the CONN-fMRI Functional Connectivity toolbox. For each seed we will conduct a seed to voxel analysis using permutation-based multiple comparisons correction at the cluster level as implemented within the CONN toolbox with white matter and CSF (but not grey matter) regressors. The primary analysis will not include global signal regression.

Resting state region of interest connectivity analysis will be performed using a priori seed regions (medial prefrontal cortex, dorsolateral prefrontal cortex, inferior frontal gyrus, insula, posterior cingulate cortex, anterior cingulate cortex, and temporoparietal junction.). Additional exploratory functional neuroimaging analysis may take place with other methodologies (e.g. measures of modularity, entropy).

**
*Libet clock task*
**

**Judgment data**

Average latencies of the W and M judgements relative to the recorded button press will be calculated for each participant. Outliers (greater than two standard deviations from participants’ mean values) will be excluded.

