### The proposed study

Taken together, this evidence suggests that psychedelics may target some of the mechanistic processes which underpin FND. Administering the psychedelic psilocybin to people with FND will allow us to probe theories of FND which postulate that it is a disorder typified by altered network connectivity across brain networks. Using a pre-post design, we will be able to test whether impaired sense of agency, changes in interoception, and dissociative phenomena are modifiable pathophysiological features of the disorder.

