### Sample size calculation

We will recruit up to 24 participants for this study. The primary aim of the study is to assess resting-state and task-based functional neuroimaging changes. Based on a previous fMRI study of the effect of psilocybin on resting-state connectivity obtained by fMRI, a mean response in connectivity in the default mode network (a connectivity network of interest) of 2.48 (arbitrary units) and a standard deviation of 2.60
^
84
^ was found in pre versus post psilocybin within-subjects analysis; this signifies an anticipated minimum detectable effect size of 0.95. For a two-tailed test and an alpha of 0.01 (to account for multiple testing) and with a power of 0.90, a total sample size of n=20 is required. An additional four participants will be recruited given expected dropouts.

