**fMRI correlates**

A windows of 1 second prior to the recorded button press will be selected as events of interest for the fMRI analysis. Intention versus movement trials will be contrasted at the participant level, and then qill be subsequently inputted into a paired-sample t-test to compare pre and post effects. Pre-selected ROIs will include the pre-SMA, inferior parietal lobule, and dorsolateral prefrontal cortex (see Baek
*et al*.
^
42
^).

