**Heartbeat tracking task**

Time estimation accuracy will subsequently be calculated using the following formula:

          1/4 ∑ [(1 − (|actual seconds – perceived seconds | / actual seconds)

Interoceptive accuracy will subsequently be calculated using the following formula:

     1/4 ∑ [(1 − (|actual heart-beats – perceived heart-beats | / actual heart-beats)

**
*Study and intervention feasibility parameters*
**

Feasibility parameters will be assessed using descriptive statistics and confidence intervals. We will assess the rate of consent of eligible patients, study retention, loss to follow-up, the acceptability of psilocybin and deviations from study protocol. Confidence intervals will be estimated where appropriate.

Participant demographic and clinical characteristics will be summarised at baseline. Patterns of missing data or nonattendance will be described for the outcome at measurement time- points and reasons for drop-out. Statistics derived will be means and standard deviations or medians, minimum, maximum, and interquartile range for continuous measures.

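### The behavioural agency and interoception tests state no use of the comparison conditions the trial already collects (M judgements, time estimation), so a general gain on either task could be read as a specific change

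*Protocol article*

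**What the plan says.** All places are in the protocol article.

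- **Claim.** The proposed study: "Using a pre-post design, we will be able to test whether impaired sense of agency, changes in interoception, and dissociative phenomena are modifiable" features of the disorder. The design is a single open-label group measured before and after dosing, with a target of 20 completers.
- **General test.** Analysis, Statistical measures: "Pre-post changes analysed using paired t-tests". The same paragraph adds "Alpha will be set at 0.05" and promises post-hoc correction for multiple comparisons.
- **Libet behaviour.** Judgment data: "Average latencies of the W and M judgements relative to the recorded button press will be calculated for each participant". Outlier exclusion follows, and nothing more. Under Neuroimaging task, W (felt urge) and M (actual press) use the same clock, button press and ball-return response. They differ only in what is judged.
- **Libet imaging.** fMRI correlates: "Intention versus movement trials will be contrasted at the participant level", and the result then enters a paired pre-post test.
- **Heartbeat task.** Heartbeat tracking task: "Time estimation accuracy will subsequently be calculated using the following formula". A formula of the same form follows for interoceptive accuracy. Under Interoception task, time estimation comes after heartbeat tracking and is otherwise run in the same way, with different interval lengths. No use of the time-estimation score is stated.

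**The concern.** With no comparator arm, a pre-post change in W latency or heartbeat accuracy mixes any specific effect with whatever else differs at a second sitting: familiarity with the clock, better attention, steadier counting. The M judgement and the time-estimation task share much of that task demand but not the intention or the heartbeat. They are the safeguard already in the data. The article uses the first for the imaging readout of the Libet task but not for its behavioural readout, and it scores the second without giving it a purpose.

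At stake is the interpretation of two mechanistic claims, that agency and interoception are modifiable. A shift that also appears in M or in counting seconds would not support either claim, and the stated tests would not show the difference.

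**Working it through.** **1. The plan's own figure.** The sample size rests on default mode network connectivity: 2.48 / 2.60 = 0.954, stated as 0.95. The Sample size calculation section sets alpha at 0.01, two-sided, and concludes: "with a power of 0.90, a total sample size of n=20 is required". Exact paired-t power from the noncentral t distribution, with df = n − 1 and noncentrality d√n, gives 0.902 at n = 20 and d = 0.95. The stated n reproduces. It concerns resting-state connectivity and says nothing about the Libet or heartbeat scores.

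**2. Inputs for the illustration.** From the article: n = 20 and a paired t-test; alpha 0.05 (Analysis) and 0.01 (Sample size calculation) serve as two reference levels. The article gives no SD of change, practice shift or correlation between conditions for either task. These are assumptions, shown as ranges, with equal SDs of change in the target and comparison conditions.

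**3. Bare test with no specific effect.** If a non-specific shift moves the target score by s SD of its change, the rejection rate is the two-sided noncentral-t tail with noncentrality s√20.

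| s | s√20 | alpha 0.05 | alpha 0.01 |
|---|---|---|---|
| 0.2 | 0.89 | 13.6% | 4.0% |
| 0.3 | 1.34 | 24.7% | 8.9% |
| 0.4 | 1.79 | 39.7% | 17.4% |

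**4. Difference contrast.** If the comparison condition shifts by c·s, the contrast shifts by s(1 − c).

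- Fully shared (c = 1): the shift is zero and the rate returns to alpha.
- Half shared (c = 0.5) with s = 0.5: 0.25 SD remains, and at alpha 0.05 the rejection rate is 11.7% to 32.4% as the correlation r of the two changes runs from 0 to 0.75.
- Not shared (c = 0): nothing is removed.

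**5. Precision cost.** The SD of the contrast is √(2(1 − r)) times the bare SD. The last column is power for a true target-only effect of 0.5 SD at alpha 0.05; the bare test has 56.5%.

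| r | SD ratio | Power of contrast |
|---|---|---|
| 0 | 1.41 | 32.4% |
| 0.25 | 1.22 | 41.1% |
| 0.5 | 1.00 | 56.5% |
| 0.75 | 0.71 | 85.1% |

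Subtraction costs power below r = 0.5 and gains it above.

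**6. Covariate form.** Regress the heartbeat change on the time-estimation change with slope b, and test the intercept, i.e. the expected heartbeat change at zero time-estimation change. A fully shared shift s then leaves s(1 − b). With equal SDs b equals r, so at r = 0.5 a shift of 0.4 SD leaves 0.4 × 0.5 = 0.2 SD. A mean-centred covariate leaves the mean change untouched and removes nothing. The nominal rate in step 4 therefore belongs to the difference, not to the covariate.

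**7. Scale of the heartbeat scores.** Each trial scores 1 − |actual − perceived| / actual. A count of 2.5 times the actual number gives 1 − 1.5 = −0.5, so the scores are not bounded at 0 and extreme over-counts can dominate a raw difference.

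**The case against.** **The contrast may be intended.** The Judgment data and Heartbeat tracking task sections are scoring steps. The general paired-t rule would also be met by a test on W minus M, and this is a condensed article. That stands in part: a reader might infer that the plan fixes separate bare tests of W and of heartbeat accuracy, but the article does not say so expressly. What remains is that it spells out the contrast for the imaging readout and not for the judgements of the same task, and leaves the time-estimation score without a use.

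**Practice and expectancy are not ignored.** The heartbeat task has a practice trial and two alternative interval sets, and expectancy (SETS) is to be related to outcome changes. This stands as partial mitigation. A practice trial does not rule out learning between sessions, and an association with SETS does not remove a mean shift.

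**Expectancy cannot simply be subtracted.** A reader might infer that the comparison conditions would clear expectancy out. They would not: expecting to be more in touch with one's body or intentions need not affect M judgements or counting seconds.

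**The tasks are only roughly matched.** Time estimation always comes second and uses different intervals. This is right, and it argues against making a raw difference the main heartbeat test.

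**The percentages are assumed.** A reader might take 14% to 40% as the trial's false-positive rate. The documents support no such figure: the shifts are assumed, and the upper range uses alpha 0.05 before the promised correction.

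**The primary endpoint is unaffected.** The Libet item named there is task-based imaging, for which the contrast is already specified. This is correct and limits the severity.

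**Conclusion.** The point holds as a cheap improvement to the behavioural analysis, at low to moderate severity. The article states paired pre-post tests and no comparator role for M judgements or time estimation, while it uses the intention-versus-movement contrast for imaging. A general task gain could therefore be reported as a change in agency or interoception.

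The size depends on a non-specific shift that the documents do not give. If that shift is 0.2 to 0.4 SD of change, the bare test rejects in 14% to 40% of trials with no specific effect at alpha 0.05, or 4% to 17% at 0.01. The difference contrast keeps the nominal rate only if the shift is fully shared. The gain is smaller with partial sharing and nil with none. The article's text does not support the conclusions that a wrong test has been fixed, that expectancy could be fully removed, or that the imaging endpoint is compromised.

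**What to change.** 1. **Agency.** State that the behavioural test is the pre-post change in mean W minus mean M, matching the imaging analysis.
2. **Interoception.** Test the change in interoceptive accuracy with the change in time-estimation accuracy as a covariate. Enter it uncentred and test the intercept (working, step 6). Give the change in heartbeat minus time-estimation accuracy as a sensitivity analysis.
3. **Reporting.** Give the W, M, heartbeat and time-estimation changes separately with 95% confidence intervals, so that a shared shift is visible.
4. **Interpretation.** Base the agency and interoception claims on these analyses. Say that they remove only shifts common to both conditions, and that expectancy specific to bodily awareness or intention remains.

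The cost is analysis wording, with no new data or visits. Intervals from subtraction are wider if the two changes correlate below 0.5 (SD ratio 1.41 at r = 0, 1.0 at r = 0.5) and narrower above that.

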**fMRI correlates**

A windows of 1 second prior to the recorded button press will be selected as events of interest for the fMRI analysis. Intention versus movement trials will be contrasted at the participant level, and then qill be subsequently inputted into a paired-sample t-test to compare pre and post effects. Pre-selected ROIs will include the pre-SMA, inferior parietal lobule, and dorsolateral prefrontal cortex (see Baek
*et al*.
^
42
^).

**Heartbeat tracking task**

Time estimation accuracy will subsequently be calculated using the following formula:

          1/4 ∑ [(1 − (|actual seconds – perceived seconds | / actual seconds)

Interoceptive accuracy will subsequently be calculated using the following formula:

     1/4 ∑ [(1 − (|actual heart-beats – perceived heart-beats | / actual heart-beats)

**
*Study and intervention feasibility parameters*
**

Feasibility parameters will be assessed using descriptive statistics and confidence intervals. We will assess the rate of consent of eligible patients, study retention, loss to follow-up, the acceptability of psilocybin and deviations from study protocol. Confidence intervals will be estimated where appropriate.

Participant demographic and clinical characteristics will be summarised at baseline. Patterns of missing data or nonattendance will be described for the outcome at measurement time- points and reasons for drop-out. Statistics derived will be means and standard deviations or medians, minimum, maximum, and interquartile range for continuous measures.

### End of study

The study is expected to be open for recruitment for two years. The total duration of a participant’s involvement in the study will vary between 15 and 22 weeks, dependent on the length of the (clinically flexible) Screening & Preparation Phase. The follow up of participants will last for 3 months after the Dosing Visit. Ongoing care for participants will be handed over to primary or secondary care teams after this time.

### Data sharing

All shareable study data, including sharable neuroimaging data, will be uploaded to an online sharing platform hosted by King’s College London.

## Discussion

This study will likely be the first in the modern era to administer psychedelics to people with FND. The primary aim is to assess functional neuroimaging changes following psychedelic administration. This may help us to further understand the complex pathophysiology underpinning FND, which is currently poorly understood
^
5
^. Additional putative mechanistic aspects of FND, such as dissociation, interoception, and agency will also be explored, and administration of psilocybin will allow us to probe whether these are modifiable targets.

Drug-facilitated therapy is current under review for a number of neuropsychiatric disorders, and there has been some emerging evidence that people with FND may respond to (es)ketamine therapy, which sometimes includes a psychotherapeutic component
^
133–
135
^. Response may be based on the ability of ketamine to disrupt brain networks or modify the top-down priors implicated in the disorder.

Pharmacological therapies are generally not specifically recommended for FND, however drug facilitated psychological
^
15
^ and physiotherapeutic
^
14
^ interventions do have a small evidence base in the disorder. The present study is not equipped to answer clinical questions about the efficacy of psychedelics; however, it may offer preliminary information about whether drug-facilitated psychotherapy is safe and feasible in this patient population.

## Data Availability

No data are associated with this article.
